### Intervention and monitoring

#### Intervention arm

Patients in the intervention arm will receive care from a PKNS for any medical (non-administrative) needs tailored to their necessities and standard medical treatment. A PKNS from each site will follow the patients enrolled.

- *PROACTIVE monitoring*: At baseline (V1), the PKNS contacts the patient to create a personal record using a semi-structured interview, including all symptoms of motor and non-motor characteristics and the type of risks that may occur. The PKNS instructs on risk prevention strategies related to the most relevant issues reported. After the initial proactive call to V1, PKNS will provide intermediate contacts every 3 months. At intermediate calls (V2, V3, V4), the PKNS focuses the interview on the problems/risks detected at baseline and provides tailored counseling and education. At the final visit (V5), the investigator will complete the follow-up of all the incident events and medical issues occurred during the study.- *REACTIVE monitoring*: During the study period, the patient and care provider may contact the PKNS at any time prior to the previously scheduled in-person visit for urgent needs by telephone (3h/day, 5 days/week, Mon-Fri) or by e-mail (within 48 h).

The PKNS can (1) also address the specific problem by interacting with the participant’s primary care physician and other healthcare providers or (2) refer to the treating neurologist (who is not the blind rater) for teleconsultation or in-person visit, according to a semi-structured algorithm that assigns four levels of priority similar to emergency room “triage”.^
19
^ Briefly, whenever a referral to a neurologist is needed, PKNS assigns a 4-level code triage, where increased urgency would lead to reduced assessment time and the opportunity for a teleconsultation with an experienced neurologist. We proposed this approach to triage patients query during COVID-19 pandemic, including a detailed flowchart.^
19
^ The code colors are summarized in Table 1. In this project, we have elaborated the “*case manager triage*” process by creating a semi-structured interview based on (1) the timing of the new event, and (2) the type of motor or non-motor issue. The code assignment is based on two step questions: (a) Does this change increase the risk of short-term morbidity (e.g., risk of hip fracture due to falls)? (b) Has functional independence changed? According to the answers to questions “a” and “b”, there will be four scenarios: (1) code white (answer: no/no): non-urgent, resolvable via e-mail/phone; (2) green code (answer: no/yes): not urgent but requires teleconsultation; (3) code yellow (answer: yes to “a”): timely teleconsultation to resolve urgent matters and decide whether an in-person visit is necessary; and (4) code red: need for hospitalization. The total scores suggest the code assignment (Table 2).

**Table 1. table1-17562864241299347:** Triage performed by the nurse specialist when the patient query needs to be addressed by the neurologist.

Triage code^ a ^	Severity	Action	Aim	Timing
White	Non-urgent	E-mail or Telephone call	Solve the query	3 working days
Green	Non-urgent	Teleconsultation	Solve the query	10 working days
Yellow	Urgent	Teleconsultation	Solve the query Decide if in-person visit is needed	3 working days
Red	Urgent	Immediate telephone call Schedule in-person visit	Urgently solve the query	1 working day

a The code assignment is based on two step questions: (a) Does this change increase the risk of short-term morbidity? (b) Has functional independence changed? See the manuscript (page 7, lines 16–22) for details and Table 2 for the scoring system.

**Table 2. table2-17562864241299347:** Triage code color assignment based on the timing and severity of motor and non-motor issue.

Timing/Frequency	Scoring	Partial score
Timing of event		
<7 days	3	
7–30 days	2	
>30 days	1	
None	0	
Falls		
Every day	4	
1–2 times/week	2	
1–2 times/month	1	
None	0	
Dysphagia		
Almost every meal	4	
Once/week	2	
Occasional	1	
None	0	
Constipation		
<1 evacuation/week	4	
2–3 evacuation/week	2	
Occasional issue	1	
None	0	
Orthostatic Hypotension		
Every day	4	
1–2 times/week	2	
1–2 times/month	1	
None	0	
Nocturia		
⩾3 times/night	4	
1–2 times/night	2	
Occasional	1	
None	0	
Pain		
Every day	4	
1–2 times/week	2	
1–2 times/month	1	
None	0	
Agitation/Psychosis		
Continuous (day and night)	4	
Every day, only certain times, manageable by caregiver	3	
Every day, only certain times, not manageable by caregiver	2	
Occasional	1	
None	0	
Total score		
Code		
White		⩽2
Green		3–6
Yellow		7–12
Red		⩾13

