### Study state

Recruitment started on August 11th 2023, and it is planned to be completed by November 17th 2024. Recruitment and the trial status are active and ongoing.

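### Table 2 gives daily agitation/psychosis that the caregiver cannot manage a lower triage score (2) than the same symptom when it can be managed (3)

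*Protocol article*

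**What the plan says.** In the intervention arm, the parkinsonism nurse specialist (PKNS) triages queries that go on to the neurologist: "whenever a referral to a neurologist is needed, PKNS assigns a 4-level code triage". The Intervention arm section adds that greater urgency should mean a shorter wait.

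Table 1 sets the response times: white 3, green 10, yellow 3 and red 1 working day(s). Table 2 sums one timing item and seven symptom items. Its bands are white ≤2, green 3–6, yellow 7–12 and red ≥13.

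The agitation/psychosis item in Table 2 has five levels. The second highest, worth 3 points, is the row "Every day, only certain times, manageable by caregiver". The level beneath it is worth 2 points and has the same frequency, but the caregiver cannot cope: "Every day, only certain times, not manageable by caregiver". Round-the-clock symptoms are worth 4 points, an occasional problem 1, and absence of the symptom 0.

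The text also derives the code from two questions: (a) whether short-term morbidity risk has risen, and (b) whether functional independence has changed. It then says of Table 2: "The total scores suggest the code assignment".

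**The concern.** The two middle agitation rows describe the same frequency and differ only in whether the caregiver can cope. The worse situation receives fewer points. Falls, dysphagia, constipation, orthostatic hypotension, nocturia and pain all run the other way, and the document gives no reason for an exception.

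A patient whose agitation is out of the caregiver's control can therefore be pointed to a slower neurologist response than one whose agitation is under control. This matters for patient safety and for how the intervention is delivered. According to Study state, "Recruitment and the trial status are active and ongoing", so the rows may already be in use.

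Two smaller ambiguities sit beside it. No sentence says whether the two questions or the score prevails when they disagree. Red is also described in two ways: "code red: need for hospitalization" in the text, and "Immediate telephone call Schedule in-person visit" in Table 1.

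**Working it through.** **Inputs.** From Table 2: timing 3 (<7 days), 2 (7–30 days) or 1 (>30 days); six other symptom items, each 0, 1, 2 or 4; agitation 2 (not manageable) or 3 (manageable); and the colour bands. From Table 1: the response times.

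**Where one point matters.** Let S be timing plus the six other symptom items. The unmanageable case totals S + 2 and the manageable case S + 3. With timing of at least 1, the codes differ only where S + 2 is the top of a band:

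| S | Not manageable (S + 2) | Manageable (S + 3) |
|---|---|---|
| 4 | 6: green, 10 working days | 7: yellow, 3 working days |
| 10 | 12: yellow, 3 working days | 13: red, 1 working day |

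S = 0 would give white against green, but it needs timing scored as none, and white has the shorter response time. It is left out.

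**Agitation alone.** S = 3, 2 or 1, so the totals are 5, 4, 3 (not manageable) and 6, 5, 4 (manageable). All are green: 0 of 3 change.

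**One other symptom.** There are 3 timings × 6 items × 3 non-zero levels = 54 combinations. S = 4 arises from 3 + 1 or 2 + 2, each for 6 items, giving 12. S = 10 is out of reach, since the maximum is 3 + 4 = 7. So 12 of 54 change (22%), all yellow to green.

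**Two other symptoms.** There are 3 × 15 pairs × 9 = 405 combinations.

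- S = 4: timing 2 with levels (1,1) gives 15; timing 1 with (1,2) or (2,1) gives 30. Together 45, yellow to green.
- S = 10: timing 2 with (4,4) gives 15, red to yellow.

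So 60 of 405 change (15%).

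**All combinations.** 3 × 4⁶ = 12,288. Changes by number of other symptoms:

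| Other symptoms | Changes / combinations |
|---|---|
| 0 | 0 / 3 |
| 1 | 12 / 54 |
| 2 | 60 / 405 |
| 3 | 260 / 1,620 |
| 4 | 495 / 3,645 |
| 5 | 300 / 4,374 |
| 6 | 47 / 2,187 |
| Total | 1,174 / 12,288 (9.6%) |

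Of the 1,174, 77 go from yellow to green and 1,097 from red to yellow. All but 72 (12 + 60), that is 1,102, need three or more other symptoms.

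**After swapping the scores.** At S = 4 the unmanageable case totals 4 + 3 = 7 (yellow). At S = 10 it totals 10 + 3 = 13 (red). It then never receives a lower total than the manageable case.

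**Questions against score.** Daily falls as the only problem score 3 + 4 = 7 (yellow) at <7 days, 2 + 4 = 6 (green) at 7–30 days and 1 + 4 = 5 (green) at >30 days. If the nurse answers yes to question (a), whose own example is hip fracture from falls, the code is yellow at any duration.

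**The case against.** The strongest reply is that the score does not fix the code. The text bases assignment on the two questions, and the total only suggests it. A nurse facing recent daily agitation that the caregiver cannot manage may well answer yes to (a) and reach yellow whatever the total. A slower response needs the other items to sum to exactly 4 or 10 and a nurse who follows the score. This is true and limits the harm, but guidance that points the wrong way is still wrong.

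The counts weight all combinations equally, most changes need many symptoms, and only 77 of 12,288 (0.6%) produce the 3-to-10-day delay. That also stands. The counts show where the code changes, not how often it will. Dementia is an exclusion criterion, and no figure is given for how often agitation prompts a call.

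The order may be a slip in the article only, with a correct working form at the sites. That cannot be excluded, so the look-back should depend on what the form shows. It is not an artefact of text extraction: each label sits on one line with its score, and the scores run 4, 3, 2, 1, 0.

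On the secondary points, the wording does imply that the questions rank above the score, and the two descriptions of red can be read as a criterion and a first action. These are clarifications that would not merit a comment on their own.

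**Conclusion.** The concern holds. As printed, Table 2 ranks the less severe agitation state above the more severe one, against the direction of every other symptom item and of the triage itself. The size is one point. It costs a code level when the other items sum to 4 (3 to 10 working days) or 10 (1 to 3 working days), and nothing otherwise.

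The conclusion about the printed table is firm. Any effect on care rests on two assumptions: that the nurses' form has the same order, and that nurses act on the suggested code. The defect is confined to neurologist referrals in the intervention arm. The proactive calls, sample size and primary analysis are not touched. It should be fixed because it concerns the safety of frail patients in an active trial.

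**What to change.** - Swap the two scores in Table 2: not manageable by the caregiver = 3, manageable = 2.
- Check the nurses' working form. If it has the same order, send the corrected table to the four sites and re-check queries already triaged with either row.
- In the same correction, add one sentence stating that the two questions and the need for hospitalisation prevail over the score, or that the higher code applies. Align the description of red in the text with Table 1.

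The cost is two numbers, one sentence, one wording change and a notice to the sites, plus a limited look-back if the form is affected. Sample size, outcomes and analysis do not change.

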#### Control arm

Patients in the control arm will undergo a 30-min in-person visit with the neurologist at baseline (V1), 6 months (V3), and 12 months (V5) after randomization.

### Procedures

#### Clinical assessment

After the screening visit (eligibility verification according to inclusion and exclusion criteria, informed consent collection, demographic data collection, and clinical data collection, including the CFS), in-person assessment with the blind rater will be performed at baseline (V1) and after 6 months (V3) and 12 months (V5), regardless of allocation arm. All study visits are conducted by neurologists experienced in movement disorders.

The study flowchart is summarized in Figure 1.

**Figure 1. fig1-17562864241299347:**
[figure not shown]
Study design. *Blood Pressure (BP) and Heart Rate (HR) are measured in the supine position and after 3 min of active standing. ADL, Activities of Daily Living; CFS, Clinical Frailty Scale; CIRS, Cumulative Disease Rating Scale for Geriatrics; EQ-5D-5L, European Quality of Life 5 dimensions; FOG-Q, Freezing of Gait Questionnaire; H&Y, Hoehn and Yahr; IADL, Instrumental Activities of Daily Living; MDS-UPDRS, Movement Disorder Society-sponsored revision of the Unified Parkinson’s Disease Rating Scale; MMAS, Morisky Medical Adherence scale-8 items; MSA, Multiple System Atrophy; NMSS, Non-Motor Symptoms Scale; PDQ-39, Parkinson’s Disease Questionnaire-39; PSP, Progressive Supranuclear Palsy; PSPRS, Progressive Supranuclear Palsy Rating Scale; UMSAR, Unified Multiple System Atrophy Rating Scale; ZBI, Zarit Burden Interview scale.

At baseline (V1) and 12 months (V5), the blind rater will collect: demographic and social information (including caregiver’s relationship with the patient (e.g., spouses, siblings, hired caregivers, etc.) and the number of caregivers per patient), general and neurological examination; PD Questionnaire-39 (PDQ-39);^
20
^ Movement Disorder Society-sponsored revision of the Unified PD Rating Scale (MDS-UPDRS);^
21
^ Hoehn and Yahr stage (H&Y); Freezing of Gait Questionnaire (FOG-Q);^
22
^ Unified MSA Rating Scale (UMSARS) in patients diagnosed with MSA or PSP Rating Scale (PSPRS) in patients diagnosed with PSP;^23,24^ Non-Motor Symptoms Scale (NMSS);^
25
^ Activities of Daily Living (ADL, IADL);^26,27^ Zarit Burden Interview scale (ZBI);^
28
^ European Quality of Life 5 dimensions (EuroQoL);^
29
^ Cumulative Disease Rating Scale for Geriatrics;^
30
^ Morisky Medical Adherence scale-8 items (MMAS-8).^
31
^ All patients and care providers will be trained on using the wearable sensor and its free downloadable app on their smartphones at the screening assessment and, to confirm understanding, at the baseline visit. At follow-up after 6 months (V3), the blind rater will perform a neurological examination, record any incident medical events (including falls) and hospitalizations, and collect PDQ-39.

#### Objective monitoring of motor function

To achieve objective and quantitative measures of patients’ motor function, we will perform a long-term monitoring of gait through continuous gait monitoring, we will use a single wearable sensor (STAT-ON^®^) SENSE4CARE SL., Cornellà de Llobregat (Spain) on a waist. STAT-ON is a Class IIa inertial medical device that is both lightweight and compact (86 g; 9 × 6.3 × 2.1 cm).^
32
^ It has successfully passed electromedical equipment tests, including those for home use. The device features two ultra-low triaxial nano-accelerometers, two microcontrollers, and a Bluetooth low-energy system, offering a battery life of 7 days under normal conditions. STAT-ON^®^ provides standard spatiotemporal gait parameters and uses advanced machine-learning algorithms to automatically detect motor patterns indicative of freezing of gait (FOG) and falls.^
33
^

In this study, following the sensor configuration based on individual clinical data (e.g., age, leg length), all patients will wear the STAT-ON sensor on the left waist via an elastic belt for five consecutive days (for 8 h per day during waking hours) per month. Recording sessions will be acquired monthly for a period of 12 months to collect the following spatiotemporal gait parameters and incident events: (1) number of steps; (2) step length; (3) step velocity; (4) step cadence; (5) number of FOG episodes; and (6) number of falls.^
34
^ Every 3 months, an encrypted and anonymized version of all collected data will be automatically sent to the PKNS of each center. The collected data will be summarized in a special report, including a graphical representation of the mean trend of parameters and spatiotemporal events of gait over time, as well as quantitative measures. In the intervention arm, physical activity levels and real-life motor autonomy will be objectively assessed to support proactive monitoring by the PKNS, who will add this objective information to the patient’s subjective report to adjust counseling and education during proactive calls made every 3 months. In the control group, data will be collected as a secondary outcome measure for final statistical analysis. At the end of the study, the data obtained from the wearable devices will be used to perform between-group analysis (comparison of cases vs controls) and within-group analysis (changes between V1 and V5 in each study group).

### Outcome measurements

#### Primary outcome

The primary aim is to demonstrate that an integrated care delivery model coordinated by a PKNS results in more favorable changes in quality of life at 12 months than standard medical care. The outcome measure will be the change from baseline to 12-month result in PDQ-39 total score, comparing cases to controls. PDQ-39 scale is a comprehensive assessment battery composed of 39 items grouped into eight subscales (mobility, activities of daily living, emotional well-being, stigma, social support, Cognition, Communication, and Bodily discomfort). Each item scores from 0 (never) to 4 (always); subscale scores and a summary index representing the global health-related quality of life can be obtained. PDQ-39 does not present any relevant ceiling or floor effect and has been demonstrated to be consistent, reliable, and discriminative for disease severity.^
35
^

#### Secondary outcomes

1. To evaluate the feasibility and effectiveness of an innovative telenursing approach consisting of proactive and reactive remote monitoring aimed at optimizing continuity of care by improving motor and non-motor disability control, including through better adherence (compliance) to the prescribing regimen. Outcome measures will be the changes in MDS-UPDRS (Parts I, II, and III) and NMSS scores in all participants. Disease-specific scales will also be used: (a) UMSARS in subjects diagnosed with MSA and (b) PSPRS in those diagnosed with PSP. In addition, changes in scores on the functional disability (CFS) and autonomy in activities of daily living (IADL, ADL) scales will be used. Compliance to prescribing regimen will be measured by the changes in scores on the Italian version of the MMAS-8 on adherence to pharmacological therapy.^
31
^2. To investigate the cost-effectiveness of the management model by telenursing compared to standard care in terms of (a) reducing the number of unplanned hospital admissions and (b) reducing complications/comorbidities to minimize direct and indirect costs to the national healthcare system. We will analyze differences between the two study groups in the number of unplanned hospital admissions in 12 months through an interview to patient and/or care provider (calculating outpatient visits, emergency room admissions, hospitalizations directly or indirectly associated with neurological pathology). In addition, differences between the two study groups in comorbidity frequency (total events, disease-related events) through (a) patient and/or caregiver interview and (b) the Italian version of the Cumulative Illness Rating Scale for Geriatrics^
30
^ will be evaluated. To estimate the incremental cost per quality-adjusted life-year gain (QALY)^
29
^ change from baseline to 12 months of the EuroQoL scale total score will be analyzed.3. To evaluate the feasibility and utility of telemonitoring to improve PKNS and neurologist decision-making using a device worn at the waist for 5 days per month (8 h/day), which passively collects data on real-life motor autonomy and fall risk, including FOG episodes. Changes in gait parameters in both between-group (between-group) and same-patient (within-group) analyses will be evaluated to obtain information on changes in physical activity, motor autonomy, gait disorders (including FOG), and risk of falls.4. To reduce the risk of caregiver burnout. Changes in the ZBI on caregiver burnout^
28
^ from baseline to 12-month follow-up will be used.5. Patient satisfaction by evaluating the differences to the patient satisfaction questionnaire.

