**Methods and analysis::**

Participants will be randomized 1:1 in intervention (PKNS) and control (standard-of-care) arms. Assessments will be undertaken at baseline and after 6 and 12 months. Primary outcome measure is the Parkinson’s Disease Questionnaire 39-items scale total score. Secondary measures include the clinical scales testing motor and non-motor symptoms, caregiver burden, adherence to therapy, cumulative disease burden and the number of unplanned hospital visits/admissions during the study period. The cost-effectiveness of this method will be evaluated by using the EuroQoL-5, which estimates the incremental cost per quality-adjusted life-years gain. Real-life motor autonomy will be objectively measured by collecting waist-worn wearable data on gait parameters (automatically detecting motor patterns indicative of freezing of gait and falls) in all subjects for five consecutive days each month during the 12-month duration of the study.

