## Rationale

The aim of the IMPACT project is to measure the effectiveness of a specialized healthcare model governed by a case manager via telemedicine dedicated to coordinating the care activity offered to patients with atypical parkinsonism in comparison with the standard-of-care model in terms of improving the quality of life. To date, no study has ever reported the effectiveness of a telemedicine service managed by a PKNS who take care of the patient by telephone and follow an Integrated Care Plan (herewith defined as “Telenursing”).

The IMPACT project is designed to investigate the benefits and cost-effectiveness of an integrated patient-centered care to propose this model to stakeholders as a new pragmatic organizational model to foster continuity of care by exploiting the potential of existing care resources. This model implements a personalized telenursing-based approach with the patient at home, including through a passive telemonitoring system of the patient’s mobility and risk of falls. As an alternative to the usual clinical model of care, in this model people with parkinsonism are proactively followed remotely by a PKNS, who can prevent and minimize complications caused by the disease and/or medication side effects (e.g., falls and fractures caused by instability or orthostatic hypotension) by promoting flexible, personalized, and comprehensive care. It is expected that this telenursing-based model will simplify care delivery by reducing the incidence of complications and unplanned hospital admissions.

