Many elements of the IMPACT innovative and timely design can be widely implemented in different healthcare settings and become part of our new way of managing patients with chronic neurological diseases, including but not limited to patients with rare, atypical parkinsonism. We will use a semi-structured flowchart that the case manager follows (1) to create a “tailor-made” file of the patient on entry to the practice, (2) proactively follow up on the most relevant motor and non-motor problems to prevent complications, and (3) to use a flowchart predefined by nurses to organize incoming calls (reactive action) and define the triage code to alert the neurologist and general practitioner for activation of the multidisciplinary team. The application of new wearable sensors and advanced machine learning algorithms will objectively monitor the real-life autonomy motor in a home environment and further indicate the innovative aspect of our research project.^
15
^ Efficacy will be assessed both by estimating the improvement in quality of life and coping mechanisms related to motor and non-motor disorders and by weighing the reduction in any unplanned hospital admissions (e.g., requests for unplanned “extra” neurological visits, any hospital or emergency room admission).

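### The count labelled unplanned hospital admissions includes outpatient visits, which nurse triage can itself replace or create, so without separate analysis it would not support a claim of fewer admissions

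*Protocol article*

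**What the plan says.** Secondary outcomes, item 2, places the measure under cost-effectiveness and defines the between-arm comparison as the "number of unplanned hospital admissions in 12 months through an interview to patient and/or care provider (calculating outpatient visits, emergency room admissions, hospitalizations" related directly or indirectly to the neurological disease).

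Two other places describe the same outcome differently. The Rationale gives as examples of unplanned hospital admissions requests for extra "neurological visits, any hospital or emergency room admission". The abstract's methods paragraph calls it "the number of unplanned hospital visits/admissions during the study period".

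Under Intervention arm, the nurse may "refer to the treating neurologist (who is not the blind rater) for teleconsultation or in-person visit". White code is handled by e-mail or telephone and green by teleconsultation. Yellow means "timely teleconsultation to resolve urgent matters and decide whether an in-person visit is necessary". For red, Table 1 gives an immediate call and a scheduled in-person visit, whereas the text of the same section describes a need for hospitalisation.

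The Control arm section describes only a "30-min in-person visit with the neurologist at baseline (V1), 6 months (V3), and 12 months (V5) after randomization".

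The Rationale expects the model to "simplify care delivery by reducing the incidence of complications and unplanned hospital admissions". The Discussion repeats the expectation of fewer unplanned admissions and links it to fractures and pneumonia.

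**The concern.** An outpatient visit is not an admission, and a request for a visit is not yet a visit. The label therefore promises something narrower than its components deliver.

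The outpatient component is also the one on which the intervention acts most directly. The same need could end as a clinic visit in the control arm and as a phone call or teleconsultation in the intervention arm. Equally, triage could arrange a clinic visit that would not otherwise have taken place. To that extent the count measures how care is delivered as well as how the patient fares.

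At stake is the reading of one secondary measure, though the Rationale and Discussion both name it beside quality of life as a way to judge efficacy. If outpatient contacts are the more frequent component, they could drive the total. A lower total might then be reported as fewer admissions when none was prevented, or a real fall in admissions might be masked by visits that triage arranged.

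**Working it through.** **1. Definition against mechanism**

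| Component | Where included | Can triage change it directly? |
|---|---|---|
| Requests for extra neurological visits | Rationale | Yes: in the intervention arm the patient can take the request to the nurse |
| Outpatient visits | Secondary outcomes, item 2 | Yes: replaced by phone or teleconsultation, or arranged by triage |
| Emergency room admissions | Both | Mainly through the patient's condition or use of the nurse's line |
| Hospitalisations | Both | Mainly through the patient's condition, but see code red |

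The article does not say whether a neurologist teleconsultation or a nurse-arranged visit counts as an outpatient visit. Nor does it say that emergency and hospital admissions will be analysed apart from visits.

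**2. Expected ratio of totals**

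The article gives no rates for any component, so all rates below are assumptions, per patient-year. Let A be the rate of emergency attendances plus hospitalisations, equal in both arms, and let V_c and V_i be the counted unplanned outpatient visits in control and intervention. Then

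ratio = (A + V_i) / (A + V_c).

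For A = 0.5, V_c = 2 and V_i = 1: (0.5 + 1)/(0.5 + 2) = 1.5/2.5 = 0.60. For V_c = 1 and V_i = 2: 2.5/1.5 = 1.67. In both cases the ratio for A alone is 1.

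**3. Illustrative simulation**

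The only planned figure used is the number per arm: 82 × 0.9 = 73.8, taken as 74. Counts are Poisson with a gamma-distributed patient effect shared by both components (variance 0.5), compared by Welch t-test in 3,000 trials per row.

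| A, both arms | V_c | V_i | Ratio of totals | Total significant | A alone significant |
|---|---|---|---|---|---|
| 0.5 | 1 | 1 | 1.00 | about 5% | about 5% |
| 0.5 | 1 | 0.5 | 0.67 | about 56% | about 5% |
| 0.5 | 2 | 1 | 0.60 | about 87% | about 5% |
| 0.5 | 1 | 2 | 1.67 | about 86% | about 5% |
| 1.0 | 1 | 0.5 | 0.75 | about 38% | about 5% |
| 1.0 | 2 | 1 | 0.67 | about 72% | about 5% |
| 1.0 | 1 | 2 | 1.50 | about 73% | about 5% |

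The 5% in the last column follows from assuming no effect on A. It is not evidence that triage leaves A untouched.

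**4. Sensitivity**

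Here the test is Mann-Whitney, with A = 0.9, gamma variance 1 and 74 per arm. If 25/50/75% of extra visits go uncounted because they become teleconsultations:

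- V_c = 1: ratios 0.87/0.74/0.61, significant in about 10/25/53% of trials.
- V_c = 2: ratios 0.83/0.66/0.48, about 14/46/87%.
- V_c = 0.5: about 6/12/23%.
- V_c = 1 with A doubled to 1.8: about 7/14/29%.
- V_c = 1 with gamma variance 2: about 6/15/35%.

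**5. Masking**

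Under the base settings of step 4, suppose A falls by 40% (0.9 to 0.54) while triage raises visits from 1 to 1.36. The totals are 0.9 + 1 = 1.9 and 0.54 + 1.36 = 1.9, so the ratio is 1.00. The total is significant in about 5% of trials, and A alone in about 41%.

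**The case against.** The strongest reply is that the article lists components without saying that they are added into one test. The word introducing the list could mean that each is tabulated, and component reporting may be in an analysis plan that is not shown. This stands in part: a single summed test is an inference. But the text names one number under an admissions label and states no separate analysis.

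Second, a reader might infer that teleconsultations go uncounted in the intervention arm, or that visits arranged by the nurse count against it. No section says either. On the Rationale's wording about requests, a query could count however it is resolved. What stands is that the rule is not stated and that the answer moves the count.

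Third, visits belong to the declared target. The measure sits under a cost aim, the Background lists unnecessary consultations among the problems, and the abstract's label includes visits. This stands, and it rules out saying that visits must be dropped or that the outcome answers no stated question. Fewer clinic visits may be a real benefit, but it is a different benefit from fewer admissions.

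Fourth, emergency and hospital counts are not wholly free of triage, because the text ties code red to hospitalisation. That also stands.

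Finally, the simulated percentages depend wholly on assumed rates. The sensitivity runs show this, with some settings barely above 5%.

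**Conclusion.** The concern holds in a limited form. The count is labelled as admissions, includes outpatient visits, and is described in three different ways. Because triage exists in one arm only, an undifferentiated count could differ between arms, in either direction, without any change in admissions. By itself it would not support the claims in the Rationale and Discussion.

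A reader might go further and infer that the trial will show a false reduction in admissions. The documents do not support that: direction and size depend on event rates and a counting rule that they do not give. The ratios of 0.48 to 1.67 above are illustrations, not estimates.

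The point concerns one measure within one of five numbered secondary aims. The PDQ-39 primary outcome and the sample size of 164 are not touched. The change is still worth making, because it decides what may be said about admissions.

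**What to change.** In Secondary outcomes, item 2, keep all components but separate them:

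- Analyse unplanned emergency room attendances plus unplanned hospitalisations as the admissions measure, as one count per patient.
- Report unplanned outpatient contacts as a separate resource-use measure. Count in-person visits and neurologist teleconsultations by the same rule in both arms, and flag contacts triggered by the nurse.
- State that any conclusion about admissions rests on the first measure only.
- Align the wording in the abstract, the Rationale and the Discussion, including whether a request or only a completed contact is counted.
- Reconcile the two descriptions of code red in the Intervention arm text and Table 1, since they affect which component a red-code contact falls under.

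The cost is wording, one further table, and recording of teleconsultations by type in both arms. The admissions measure will have fewer events and so less precision. Since recruitment is under way, the change should be dated and made before any comparison by arm.
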